### Exclusion criteria

Employees will be excluded from the study if they are pregnant at the time of inclusion, victims of workplace bullying, have post-traumatic stress-disorder, severe mental illness (e.g. psychosis) or any other co-morbidity that could considerably affect their ability to work and/or quality of life.

### Randomization

The study uses a two-armed cluster randomized design in which the participating consultants are randomized using computer-generated random numbers into either giving the intervention or performing care as usual. Hence, each OHS consultant has to continuously apply the same treatment within the context of this study. The randomization is stratified by OHS unit as well as by occupational category, as those two factors are assumed to have a potential impact on the results and a balance within strata is necessary.

It was not feasible to randomize employees between OHS consultants trained or not trained in the intervention, because different employers have contracts with different OHS consultants, that is, a certain employee is linked to a certain OHS consultant. An alternative may have been to train all OHS consultants in the intervention, however, this should have increased the risk of contamination.

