## Methods

### Study design and setting

The study has a two-armed cluster randomized controlled design with a primary follow-up period of 1 year (see Fig. 1). The study is conducted in collaboration with three OHSs in Sweden. One OHS has nationwide coverage while two are regional OHSs. Each participating OHS consultant is considered as one cluster. The participating OHS consultants consist of occupational nurses, physicians, physiotherapists, ergonomists, occupational health counselors and psychologists.

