### Data analysis

Statistical methods adapted for cluster randomized designs will be applied. The plan is to apply various forms of regression models and mixed models. Intention-to-treat analyses will be carried out. Where relevant, per-protocol analyses will also be performed. If it appears that potential confounders have been unevenly distributed and can be expected to affect the results when the two interventions are compared, these factors will be adjusted for in the analyses. Possible interaction effects on the outcome for (1) gender x treatment (intervention) and (2) sick leave status (sick leave/no sick leave) x treatment will be checked for. If they are statistically significant, subgroup analyses will be considered.

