#### Statistical power

Sample sizes of 75 in Group 1 and 75 in Group 2, which were obtained by sampling 15 clusters with an average of five subjects each in Group 1 and 15 clusters with an average of five subjects each in Group 2, achieve 84% power to detect a difference between the group means of at least 25.00 days of registered sickness absence 1 year after baseline. The standard deviation of subjects is 50.00. The intra-cluster correlation coefficient is 0.010. The coefficient of variation of cluster sizes is 0.650. A two-sided t-test was used with a significance level of 0.050. This test used degrees of freedom based on the number of subjects. No missing values are expected since the primary outcome is based on register data. The aim of the current study is therefore to include a total of 150 participants.

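### Whether the two stratification factors enter the primary model depends on observed imbalance; if they are prognostic and left out, the standard error is too wide and power is lost

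*Protocol article*

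**What the plan says.** The Randomization section of the protocol article gives the design and its reason: "The randomization is stratified by OHS unit as well as by occupational category, as those two factors are assumed to have a potential impact", continuing "on the results and a balance within strata is necessary".

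Study design and setting supplies the possible levels. "The study is conducted in collaboration with three OHSs in Sweden", and the consultants are "occupational nurses, physicians, physiotherapists, ergonomists, occupational health counselors and psychologists". The number of OHS units, as distinct from the three OHSs, is not given.

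Data analysis leaves the model open: "Statistical methods adapted for cluster randomized designs will be applied. The plan is to apply various forms of regression models and mixed models". It then states one rule for covariates. The condition is: "If it appears that potential confounders have been unevenly distributed and can be expected to affect the results when the two interventions are compared". Where that condition is met, the consequence is that "these factors will be adjusted for in the analyses". Nothing in the article says that the stratification factors enter the model, and nothing says that they are left out. The calculation under Statistical power does not use them.

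**The concern.** The two sections fit badly together. The design names two factors as likely to affect the outcome and balances them. The analysis rule then selects covariates by observed imbalance, which is what stratification is meant to prevent. Factors balanced by design would enter the primary model only when balance happens to fail.

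Two things are at stake.

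- **Pre-specification.** The content of the primary model would vary with chance features of the sample. The Blinding section says that the researchers will not know the allocation during analysis. That limits deliberate steering but does not fix the model in advance.
- **Precision.** OHS and occupation are attributes of the consultant, so any variance they explain sits between clusters. If they are omitted, that variance goes into the between-consultant component and widens the reported standard error, although stratification has already removed it from the treatment comparison. The Care as usual section describes routine care that differs between the three OHSs, which makes it plausible that OHS is prognostic.

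**Working it through.** **Inputs (Statistical power section).** 75 participants and 15 clusters per arm, mean cluster size m = 5, CV of cluster size 0.65, ICC 0.010, SD 50 days, difference 25 days, two-sided alpha 0.05, degrees of freedom based on subjects (148).

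**1. The plan's own figure.** Design effect = 1 + ((CV² + 1)m − 1) × ICC = 1 + (1.4225 × 5 − 1) × 0.010 = 1.061. SE = 50 × √(2 × 1.061/75) = 8.41 days. A noncentral t with 148 df gives 83.97%, so the stated 84% reproduces. With cluster-level df (30 − 2 = 28) it is 81.8%.

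**2. Case A: the ICC of 0.010 is unconditional and already contains the strata.** Between-consultant variance is 0.010 × 2500 = 25, so the strata can explain at most 1% of the total. Adjustment uses 2 df for OHS and 5 for occupation, leaving 28 − 7 = 21. Type I error is P(|t| > 2.048 × SE ratio) with 28 df.

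| Share of between-consultant variance explained | True SE | 8.41 / true SE | Type I error, strata omitted | Power, omitted | Power, included |
|---|---|---|---|---|---|
| all | 8.12 | 1.035 | 4.3% | 82.6% | 83.5% |
| half | 8.27 | 1.017 | 4.6% | 82.2% | 82.2% |
| none | 8.41 | 1.000 | 5.0% | 81.8% | 80.9% |

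For the first row, the true SE = √2475 × √(2/75) = 8.12.

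**3. Case B: the ICC of 0.010 is what remains within strata, and the strata explain a further share R of total variance (R is assumed).** A model without strata then faces ICC = R + (1 − R) × 0.010.

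| R | ICC | Design effect | SE | Power (148 df, as in the plan) |
|---|---|---|---|---|
| 5% | 0.0595 | 1.364 | 9.53 | 74% |
| 10% | 0.109 | 1.666 | 10.54 | 65% |

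**4. Simulation of Case B.** Settings: 30 clusters, mean size 5, CV 0.65, ICC 0.010 within strata, SD 50. Clusters were allocated 1:1 within five equal strata (assumed). The model was a random-intercept REML fit with cluster-based df, and there were 1,500 runs per setting.

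| R | Mean SE, omitted / included | Type I error, omitted / included | Power, omitted / included |
|---|---|---|---|
| 0 | 8.7 / 9.0 | 4.1% / 4.5% | 77% / 74% |
| 5% | 9.5 / 8.8 | 3.3% / 3.7% | 73% / 78% |
| 10% | 10.3 / 8.6 | 2.3% / 3.6% | 66% / 80% |

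At R = 10% the unadjusted estimate actually varies with an SD of about 8.6 days, so its reported SE of 10.3 is about 20% too large.

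**5. How the imbalance rule would behave.** Stratification balances consultants, not participants. In the same simulation a simple chi-square test on participant counts flagged stratum imbalance (p < 0.05) in about 30% of trials. The article names no criterion for imbalance, so this is only an illustration, but it shows that the strata would enter in some trials and not in others.

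**6. Sparse cells.** If the two factors are fully crossed, 3 × 6 = 18 cells share 30 consultants, or 1.67 per cell. Under random spread the expected number of cells with a single consultant is 30 × (17/18)²⁹ = 5.7, and a single consultant cannot be balanced. The crossing and the category levels are assumed, because the article does not state them.

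**The case against.** **The rule excludes nothing.** A reader might infer that the analysis ignores the strata. The article does not support that. The rule concerns potential confounders in general, neither names nor excludes the stratification factors, and follows a promise of methods suited to cluster designs, which can carry stratum terms. This stands. What the article lacks is a commitment to include them.

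**Sparse strata trigger the rule.** It is also tempting to say that imbalance left by thin cells would pass straight into an unadjusted estimate. But that is when the rule applies and would bring the factors in. This stands too. The thin cells matter for how the adjustment is coded, and as a reason why inclusion would vary with chance.

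**The covariate list belongs in the analysis plan.** A condensed article may leave the full list to a plan that is not shown, and no figure in the article is wrong. This stands only in part. The article does more than stay silent: it states a rule, and that rule is ill-suited to the design described two sections after the inclusion and exclusion criteria.

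**The loss may be very small.** Cluster-level factors cannot explain more than the between-cluster variance. If the ICC of 0.010 is unconditional, that is about 1% of the total, and Case A applies. This stands as one of two possible readings, because the article does not say whether the ICC is conditional on strata.

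**Conclusion.** The concern holds in limited form. The article stratifies on two factors that it assumes to be prognostic, and its only stated adjustment rule makes their inclusion depend on the observed data.

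The error, if they are omitted, is conservative. A reader might take a misstated standard error to mean a risk of false positives. The working shows the opposite: in a cluster-adapted analysis the interval is too wide, type I error falls below 5%, and power is lost. If the strata are not prognostic there is no such error.

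The size depends on what the ICC of 0.010 means:

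- **Unconditional:** the SE is at most about 3.5% too wide, type I error is about 4.3%, and power changes by about a point or less.
- **Conditional, with the strata adding 5 to 10% of variance:** power without them is about 74 to 65% by formula (73 to 66% in simulation), against the stated 84%. With them it is 78 to 80% in simulation.

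The variance shares, and the five equal strata in the simulation, are assumptions. The article gives no estimate of either. The case for change does not rest on the larger figures: fixing the strata in the model removes a data-dependent choice at little cost.

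**What to change.** State that OHS and occupational category, with rare categories collapsed, enter every between-arm model as fixed main effects regardless of observed balance. Consultant stays as the random effect, with cluster-based degrees of freedom. Use main effects, not the up to 18 crossed cells. If units are finer than the three OHSs, say how they are grouped. Keep the imbalance rule, if at all, only for other covariates and only in sensitivity analyses. It would also help to say whether the planning ICC is conditional on the strata.

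The change is one sentence and needs no new data. It uses up to about 7 of 28 cluster-level degrees of freedom. If the strata turn out not to be prognostic, the price is about 1 point of power by formula (81.8% to 80.9%), or about 3 points in the simulation (77% to 74%).

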### Blinding

The employees are not given information about the possibility of receiving another type of treatment within the trial. This is because the OHS consultants have been pre-randomized into delivering one of the two interventions. The researchers will not know about treatment allocation during the analyses. However, the OHS consultants are not blinded with regard to which treatment is given.

### Matched control group

An additional comparison group for those on sick leave at baseline will be obtained by means of register-based data from the SSIA. The material will be matched on the basis of diagnosis, age, sex and sick leave during the previous 3 months. This data allows for a better understanding of the development patterns of sick leave for the study participants on sick leave in both the control and the intervention groups.

### The individual and workplace-focused intervention

The OHS consultants delivering the experimental condition receive general information about the study and information about the recruitment process. After this, a 1-day training course is given by members of the research group and a clinical psychologist. Individual supervision and follow-up is thereafter provided on a continuous basis by the KI research group by email and scheduled phone calls. The OHS consultants are also offered further guidance for the intervention at 1–2 follow-up meetings after the initial training (on demand). They also receive detailed work sheets.

The theoretical basis for the intervention stems from PST [22] and the “mismatch” model concerning the match between the employee and the work environment [23]. This mismatch model emphasizes six aspects of the work situation which are addressed during the meetings: workload, control, reward, community, fairness and values. A participatory approach is applied by which the supervisor and the employee are guided by the OHS consultant and encouraged to actively take part in problem solving concerning the work situation [14, 24].

As outlined in Fig. 2, the intervention comprises two interviews, one of which is held with the employer (usually the nearest supervisor) and the other with the employee, and a third session at which both the employer and the employee are present [14, 24]. This third dialogue aims to facilitate a closer match between the employee’s expectations and abilities and the job situation. The order in which the two separate interviews are held depends on the internal logistics at the OHS.

**Fig. 2 Fig2:**
[figure not shown]
Overview of the intervention

The interview with the employee’s supervisor covers any earlier measures taken by the employer for the employee and the supervisor’s view of the “causes” of the employee’s stress or poor mental health. The supervisor is also asked about what he/she considers to be the most important problem to address to promote the employee’s work ability or RTW. For practical reasons this meeting usually takes place over the phone and lasts about 15 to 30 min. The same themes are discussed during the interview which takes place in person between the OHS consultant and the employee. However, this session is more comprehensive and also includes an initial section concerning the private situation of the employee, work-family balance, and a survey of possible mismatches between the employee and the job situation [23]. A problem-solving approach is also initiated. This interview takes approximately 90 min.

The problem-solving approach is guided by the following steps (1) goal setting and problem definition – the problem is specified in detail including when and where it happens as well as how it is expressed, (2) generation of possible solutions, (3) decision making about solutions, including potential consequences of different solutions, (4) setting up an action plan, including implementation of prioritized solutions.

During a third meeting the supervisor, employee and the OHS consultant meet face-to-face and focus on problem definition and possible solutions for promoting work ability or RTW. At this meeting the supervisor’s and the employee’s views of the problem are discussed with the aim of achieving a convergence of views. Relevant external parties such as an OHS physician or a representative of the Social Insurance Agency may also participate in this meeting if deemed necessary. The main task of the OHS consultant during the third meeting is to help the employee and his/her supervisor to reach specific problem definitions and feasible solution(s) to be implemented at the workplace to improve work ability or facilitate RTW. The suggested solutions and their follow-up are registered in an action plan by the OHS consultant. It is crucial that both the employee and the supervisor are encouraged to understand, and to be active and participatory in, the problem-solving process and that consensus between the parties is reached on possible solutions to facilitate RTW or manage stress at the workplace.

The OHS consultant is recommended to conduct regular follow-ups of the supervisor and the employee by phone calls or meetings in accordance with an agreed schedule. At least three follow-ups during the 3 months following the third session are recommended. These follow-ups focus on the action plan and whether planned measures have been undertaken; progress and possible new problem solving. In addition to the planned intervention, the OHS may also refer the employee to other services or measures in accordance with routine practice.

### Care as usual

The OHS consultants delivering the control condition receive information about the recruitment process followed by a general introduction to research into psychosocial factors and mental health at work. In total this takes 2 h.

The OHS consultants then continue to deliver the routine care throughout the study period. At the three OHSs where the current study is being performed, care as usual in case of stress-related symptoms and CMDs usually involves both the employee and the supervisor. However, these practices do not follow the same structure as in the experimental intervention nor do they use the mismatch model as guidance for defining problem areas or the described problem-solving approach. At one of the OHSs the intervention is more focused on further medical and lifestyle factors, even though the work situation is also addressed and the employer is involved in the intervention. There is also some variance among the OHS consultants as to how this intervention is applied. One of the OHSs does not usually hold an individual interview with the employee; in other words, the joint meeting between the employee, the employer and the OHS consultant is often held directly after a short interview with the supervisor. A third OHS is about to implement the Swedish guidelines for OHSs concerning the management of mental health at work. These guidelines recommend the involvement of the employer and problem-solving techniques. However, despite the similarities with the experimental intervention the personnel delivering the care as usual have not received the same training in these methods as the consultants delivering the active intervention. A survey of the OHS consultants regarding more specific details of the contents and routines of care as usual will also be conducted as part of the study’s process analysis.

### Co-interventions

As it is difficult to avoid the possibility of co-interventions, the questionnaires sent out to the employees ask for information about supplementary treatment from the OHS or other agencies. The questionnaire assesses the type of intervention or help that was sought as well as the number of times it was received and whether it was administered by the OHS or others.

### Measurements and procedure

Data are gathered by use of registers, questionnaires and SMS text messages. Register data are collected from the SSIA. These data are based on register information, including sick-listing and sickness and activity compensation. Valid questionnaires in electronic format are administered at baseline and after six and 12 months (paper versions are available on demand). Furthermore, monthly (every fourth week) text messages asking five questions about sick leave, stress and work ability obtained from the employee are sent to the participants over a 1-year period [25]. The use of text-messages is motivated since this measurement also includes short spells of sick leave (<15 days) which are not covered by the SSIA. A 3-year follow-up of register-based data on sick leave is also planned.

### Primary outcome

#### Registered sickness absenteeism

The primary outcome is the total number of days of sickness absence during the 12-month follow-up period (including sickness benefit and disability pension). Sickness benefit and disability pension will also be analyzed separately.

### Secondary outcomes

#### Self-reported sickness absence and return to work using text messages

For those on sick leave at baseline, the time to RTW will be calculated from baseline until (1) the employee returns to work in any increased level, or (2) full return to work (working usual hours during an uninterrupted period of at least 4 weeks). The prevalence of no sick leave, part-time sick leave and full-time sick leave during the 12-month follow-up period following baseline will be presented.

#### Registered sickness absenteeism

The total number of days of registered sickness absence from the SSIA will be calculated in the same way after 3 years as at the 1-year follow-up.

#### Mental health and stress-related symptoms

Self-reported exhaustion will be assessed by the Emotional exhaustion sub-scale of the Maslach Burnout Inventory - General Survey (MBI-GS). The MBI-GS is a well-established instrument for assessing burnout [26]. Furthermore, stress-related Exhaustion Disorder is assessed by the s-ED measurement instrument [27]. The s-ED is based on diagnostic criteria for stress-related Exhaustion Disorder according to the Swedish National Board of Health and Welfare. Support has been found for its constructive and predictive validity [27]. In addition, the Hospital Anxiety and Depression Scale will be used to assess anxiety and depression among the employees [28, 29]. Finally, self-reported stress as assessed by a single item included in the text messages will be used. This has been found to be valid for monitoring stress in a work-related context [30].

#### Health problems

Sleeping problems will be measured by the insomnia subscale from the Karolinska Sleep Questionnaire [31]. Furthermore, the European Quality of Life - 5 Dimensions questionnaire (EQ-5D) will be applied to investigate health-related quality of life [32]. Self-perceived general health will be assessed by a single question (Orwelius et al. In manuscript). Presenteeism (being at work while sick) will be assessed by a single question developed by Aronsson et al. [33].

#### Work ability and working environment

Self-reported work ability will be assessed by three items from the Work Ability Index [34]. Two of the items relate to perceived capacity to work relative to the physical and mental demands of the work. The third item enquires whether the employee believes that s/he can be working at the same workplace in 2 years’ time. Two additional items are intended to measure work performance impairment due to (1) health problems and (2) problems in the working environment. These items have been developed and modified inspired by the Work Productivity Activity Impairment questionnaire - General Health Questionnaire (WPAI-GH) [35, 36]. The second item has been developed and evaluated in Sweden [35–37]. Finally, job satisfaction will be estimated by a single self-report item [38].

